# Influence of kinesiophobia on pain intensity, disability, muscle endurance, and position sense in patients with chronic low back pain—a case-control study

**DOI:** 10.1186/s13063-022-06406-6

**Published:** 2022-06-06

**Keywords:** Low back pain, Kinesiophobia, Position sense, Endurance

## Abstract

**Background:**

Patients with chronic low back pain (CLBP) frequently present with kinesiophobia. Though large body of evidence reported the impact of kinesiophobia in patients with CLBP, there are paucity of studies in associating kinesiophobia to muscle endurance and position sense in patients with CLBP. The primary aim of the study is to compare the impact of kinesiophobia on lumbar extensor endurance, position sense in patient with CLBP, and asymptomatic individuals. Secondarily, we aim to examine the association between kinesiophobia and lumbar extensor endurance, position sense, pain intensity, and functional ability in patients with CLBP. Thirdly, we aim to assess the degree of association of various factors on CLBP, lumbar endurance, and position sense.

**Material and methods:**

This case-control study will have 200 patients with CLBP and 400 controls. Kinesiophobia, lumbar endurance, and lumbar position sense will be assessed with Tampa Scale, Soren’s lumbar extensor test, and lumbar repositioning test respectively. Secondarily, the pain intensity will be assessed with visual analog scale and functional ability with Patient-specific Functional Scale in patients with CLBP. Lumbar endurance and joint position sense will be compared between subjects with and without kinesiophobia. Kinesiophobia scores will be compared with lumbar extensor endurance and proprioception joint position errors, pain intensity, and functional ability. Simple and multiple binary logistic regression will be used to determine crude and adjusted odd’s ratio for kinesiophobia, lumbar position sense and kinesiophobia, and lumbar endurance.

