Kinesiophobia may produce a wide variety of physical and psychological effects that indirectly influence back pain to be maintained or recur or cause changes in the somatosensory system [26–28]. Studies in the past reported that patients with LBP had poorer ability to sense a change in lumbar position than control subjects [29–33]. Evidence reported that higher levels of pain-related fear are significantly associated with reduced amplitudes of movement and larger muscle activity and were consistent across subgroup and moderation analyses [27, 34]. Recent systematic reviews reported a moderate to strong evidence of associations between a greater degree of kinesiophobia, disability, and poorer quality of life in CMP. However, there was lack of consensus as there was heterogeneity present between all included studies in the systematic reviews in terms of population, outcome measures, pain conditions, and statistical parameters. Hence, an efficient comparison could not be made between their included studies. Moreover, none of the included studies specifically evaluated the possible mediating effect of kinesiophobia in CMP. Furthermore, confounding variables were not always explored in all included studies [18, 35]. Recent researches exploring the influence of kinesiophobia on CLBP and its various outcome are in the infant stage.

Chronic LBP is also associated with decreased endurance of the trunk extensor muscles [TE]. In addition, studies reported TE in chronic LBP participants to be significantly weaker than asymptomatic participants. The multi-factorial dysfunctions consistently reported in literature is the deconditioning of the lumbar extensor musculature, i.e., thoracic and lumbar erector spinae, multifidus, and quadratus lumborum [36, 37].

Long-term mechanical low back pain (LBP) results in inhibition and atrophy of the deep segmental muscles such as multifidus and overactivity of the longer superficial muscles of the trunk with resultant decreased dynamic activity and increased fatigability [38, 39]. Though the muscular endurance is reported to be affected in the patient with CLBP, no studies have explored the impact of kinesiophobia on lumber muscle endurance in patient with CLBP [40, 41] against asymptomatic subjects.

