Moreover, in the spine, proprioceptive information is provided by structures present in the spinal ligaments, facet joints, intervertebral discs [42], and paraspinal muscles [43]. Muscle spindle density is high in deep paraspinal rotators, which are small muscles spanning one or two segments of the spine act as kinesthetic sensors that monitor trunk position and movement. It is these muscle receptors that are more likely responsible for information in the midrange of trunk motions [44]. Deficits in proprioception in lower back pain [LBP] have generally been attributed to impaired afference from paraspinal muscle spindle or changes to its central processing. Trials with visual feedback demonstrated that participants with and without CLBP could perform the task accurately. Yet, when visual feedback was removed, participants with CLBP matched the force less accurately than control participants and undershot the target force [42–44].

To the best of our knowledge, till date there are no studies assessing the relationship between kinesiophobia, lumbar endurance, and lumbar position sense in subjects with CLBP. Therefore, the current study aims to compare the impact of kinesiophobia on lumbar extensor endurance, and position sense in patient with CLBP and asymptomatic individuals. Secondarily, we aim to examine the association between kinesiophobia and lumbar extensor endurance, position sense, pain intensity, and functional ability in patients with CLBP. Thirdly, we aim to assess the degree of association with various factors on CLBP, lumbar endurance, and position sense. Therefore, we hypothesized that kinesiophobia would impact the lumbar position sense and lumbar endurance as well.

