### Statistical analysis

The statistical analysis will be computed using SPSS Statistics software, version 27 (IBM, Chicago, IL, USA). The data analyses will be conducted by a statistician. Continuous variables will be summarized using standard measures of central tendency and dispersion, either as mean and standard error, or median and interquartile range. Dichotomous or categorical variables will be summarized by frequencies or denominators and percentage.

Kinesiophobia, lumbar endurance, and joint position sense will be compared between patients and controls using appropriate statistical tools. Kinesiophobia scores will be correlated with lumbar extensor endurance and proprioception joint position errors, pain intensity, and functional ability. Chi-square test will be used to find the association between kinesiophobia and lumbar endurance and joint position sense. Spearman rank correlation will be used to find the correlation between kinesiophobia, pain, and functional ability. Simple and multiple binary logistic regression will be used to determine crude and adjusted odds ratio for kinesiophobia, lumbar position sense and kinesiophobia, and lumbar endurance.

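### The listed analyses do not compare the kinesiophobia effect between CLBP patients and controls as the primary aim requires, and the pooled kinesiophobia comparison is confounded by CLBP if run as written

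*Protocol article*

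**What the plan says.** The Background gives the primary aim as to "compare the impact of kinesiophobia on lumbar extensor endurance, and position sense in patient with CLBP and asymptomatic individuals"; the abstract words it in the same way. The secondary aim is limited to one group: "Secondarily, we aim to examine the association between kinesiophobia and lumbar extensor endurance, position sense, pain intensity, and functional ability in patients with CLBP".

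The analyses listed for endurance and position sense are:

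- Abstract, Material and methods: "Lumbar endurance and joint position sense will be compared between subjects with and without kinesiophobia".
- Statistical analysis: "Kinesiophobia, lumbar endurance, and joint position sense will be compared between patients and controls using appropriate statistical tools".
- Statistical analysis: "Chi-square test will be used to find the association between kinesiophobia and lumbar endurance and joint position sense". The population is not stated.
- Statistical analysis: correlations of kinesiophobia scores with both outcomes, population again not stated.
- Statistical analysis: crude and adjusted odds ratios from binary logistic regression, with no covariates named.

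The Sample size section adds that confounders will be handled by subgroup analysis, without naming the subgroups. It plans 200 cases and 400 controls, with kinesiophobia in 70% of cases and an assumed 10% of controls. The Background reports that people with low back pain have lower trunk-extensor endurance and poorer position sense.

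**The concern.** Comparing the impact of kinesiophobia in two groups takes three quantities: the effect in CLBP patients, the effect in asymptomatic people, and the difference between them. The secondary aim supplies the first. Nothing listed supplies the second or third. Patients versus controls estimates the CLBP effect. Kinesiophobic versus non-kinesiophobic estimates one overall contrast.

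That overall contrast has its own problem if it is run on all 600 participants. Kinesiophobia is expected to be far more common in cases, and cases are expected to do worse on both outcomes whatever their fear of movement. A crude comparison therefore carries part of the CLBP effect under the label of kinesiophobia. The abstract's Discussion says the results will support adding kinesiophobia assessment to the evaluation of CLBP patients. A crude pooled result could appear to support that even if kinesiophobia had no effect within either group.

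**Working it through.** **Inputs.** From the Sample size section: 200 cases, 400 controls, kinesiophobia prevalence 70% and 10%, odds ratio 2. From the Discussion: at least 80% of the sample analysed. The document gives no size for the CLBP effect, so D = 0.2 to 0.8 SD is assumed. It states neither alpha nor power; two-sided 0.05 and 80% are assumed.

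**1. The plan's own figure.** An odds ratio of 2 on a 10% control prevalence has odds 2 × 0.1/0.9 = 0.222, so the case prevalence is 0.222/1.222 = 18.2%. The two-proportion formula with a 1:2 ratio and no continuity correction gives 205 cases + 410 controls = 615, within 3% of 600. The stated 70% against 10% is a different input: (0.7/0.3)/(0.1/0.9) = 21. The two planning inputs conflict, so both are carried forward.

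**2. Cross-classification at 70%/10%.**

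| | Kinesiophobic | Not kinesiophobic |
|---|---|---|
| Cases | 140 | 60 |
| Controls | 40 | 360 |
| Share with CLBP | 140/180 = 77.8% | 60/420 = 14.3% |

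The gap in CLBP share is g = 0.778 − 0.143 = 0.635.

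**3. Spurious pooled difference.** With no kinesiophobia effect in either group, the expected pooled difference is g × D. Its standard error is √(v₁/n₁ + v₀/n₀), where v = 1 + D²s(1 − s) and s is the CLBP share in that column. For D = 0.5: difference 0.317, v₁ = 1.043, v₀ = 1.031, SE = √(1.043/180 + 1.031/420) = 0.0908, z = 3.50. The chance of a significant result is Φ(3.50 − 1.96) + Φ(−3.50 − 1.96), which is 93.8% from unrounded values.

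| Prevalence, cases/controls | g | D = 0.2 | D = 0.3 | D = 0.5 | D = 0.8 |
|---|---|---|---|---|---|
| 70%/10% (stated) | 0.635 | 29.5% | 56.5% | 93.8% | >99% |
| 50%/10% | 0.497 | 17.6% | 33.4% | 71.0% | 97.3% |
| 50%/20% | 0.317 | 10.9% | 18.5% | 41.0% | 75.9% |
| 18.2%/10% (implied by odds ratio 2) | 0.164 | 5.8% | 6.8% | 9.9% | 16.9% |

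A 4,000-run simulation at 70%/10% and D = 0.5 gave 93.8% for the crude comparison and 4.8% once CLBP group was in the model.

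**4. Binary version, for the chi-square.** Assume poor endurance in 50% of cases and 25% of controls, unrelated to kinesiophobia within group. Then P(poor | kinesiophobic) = 0.778 × 0.50 + 0.222 × 0.25 = 0.444, and P(poor | not) = 0.143 × 0.50 + 0.857 × 0.25 = 0.286. The crude odds ratio is (0.444/0.556)/(0.286/0.714) = 2.0, against a within-group odds ratio of 1.

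**5. Precision of the needed estimates at 70%/10%.** Detectable difference = (1.96 + 0.84) × SE, in SD units.

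- Within cases: SE = √(1/140 + 1/60) = 0.154; detectable 0.43.
- Within controls: SE = √(1/40 + 1/360) = 0.167; detectable 0.47.
- Group-adjusted common effect (inverse-variance combination of these two): SE = 0.113; detectable 0.32.
- Interaction: SE = √(0.154² + 0.167²) = 0.227; detectable 0.64.
- Crude pooled contrast, for comparison: detectable 0.25.

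With 80% of the sample, dividing by √0.8 gives 0.48, 0.52, 0.35 and 0.71 for the first four.

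**The case against.** A reader might infer that the plan never takes CLBP into account. It does in part: the secondary aim studies the same two outcomes within CLBP patients, where this confounding cannot arise. The plan also promises adjusted odds ratios and subgroup control of confounders. Since those covariates and subgroups are unnamed, CLBP could be among them, and a covariate list may properly sit in an analysis plan that is not shown. This stands. It rules out saying that the CLBP effect will be reported as a kinesiophobia effect.

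A reader might also infer that a false finding is almost certain. That depends on an assumed CLBP effect and on the prevalence gap. At the 18.2% implied by the odds ratio of 2, the false-positive rate stays below 17% even at 0.8 SD. Nor does the 1:2 ratio alone fix the bias. The spurious odds ratio of 2.0 equals the planning odds ratio only because 50% and 25% were chosen, and by the sample-size inputs the planning figure concerns kinesiophobia in cases versus controls.

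Two further objections have some weight. The stated hypothesis is only that kinesiophobia affects the two outcomes, which is a main effect, so a formal interaction test is one reading of the aim. And the word subjects in the abstract does not strictly say that both groups are pooled. However, the eligibility headings use that word for both groups, and the preceding abstract sentence limits pain and function to CLBP patients while the quoted one carries no such limit.

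What these points do not remove is that the stated kinesiophobia comparison and chi-square are crude as written, and that no listed analysis addresses controls or the contrast between groups.

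**Conclusion.** The concern holds in this limited form. The primary aim calls for the kinesiophobia effect to be compared between CLBP and asymptomatic people. The listed analyses include a within-CLBP look under the secondary aim, but no effect within controls, no named adjustment for group and no comparison of effects between groups. This is a mismatch between the stated aim and the stated analyses, not a complaint about detail left to another document.

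If the kinesiophobia comparison and chi-square are run on the pooled sample, they are confounded by CLBP. With the plan's 70% and 10%, the spurious difference is 0.635 times the CLBP effect. With a smaller prevalence gap the multiplier falls to 0.32 (50%/20%) or about 0.16 (18.2%/10%). The direction of the CLBP effect comes from the Background; its size is assumed, so the false-positive rates are a range and not a forecast.

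**What to change.** State in the analysis section that:

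1. the kinesiophobia effect on endurance and on position sense will be estimated separately within CLBP patients and within controls;
2. every pooled model, including the adjusted logistic models, will contain CLBP group;
3. a kinesiophobia-by-group term will be added for the between-group comparison named in the primary aim;
4. no conclusion will be drawn from the crude pooled comparison or the pooled chi-square test.

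This uses data already to be collected. The cost is lower precision, which should be stated in advance: at 80% power and 70%/10% prevalence the interaction can detect only about 0.64 SD, against 0.25 SD for the crude contrast. The weakest cell is about 40 kinesiophobic controls, or 32 if 80% of the sample is analysed. The investigators should say beforehand that a non-significant interaction will not be read as evidence of equal effects.

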**Discussion:**

The finding from this study can be generalized as this study has adequate sample size and subgroup analysis by adjusting the variables to draw a valid conclusion. The finding of this study will help the working physician to include assessment of kinesiophobia as part of musculoskeletal evaluation for patient with CLBP in a prospective diagnostic intervention.

**Trial registration:**

ClinicalTrials.gov NCT05079893. Registered on 14 October 2021.

**Supplementary Information:**

The online version contains supplementary material available at 10.1186/s13063-022-06406-6.

## Background

Chronic lower back pain (CLBP) is one of leading causes of disability for adults of working age [1]. Globally, years lived with disability caused by low back pain increased by 54% between 1990 and 2015 [2]. Chronic lower back pain is defined by the location of pain between the lower rib margins and the buttock that lasts for more than 12 weeks [3, 4]. There are several causes for CLBP, and the differential diagnosis can be challenging. Specific causes for LBP compromises 15% of all back pain caused by a specific pathophysiologic mechanism, such as herniated nuclei pulposus, infection, osteoporosis, rheumatoid arthritis, fracture, or tumor [5–7]. The majority of remaining patients are labelled as having nonspecific low back pain [NSLBP]. Because NSLBP does not have pathoanatomical cause, treatment focuses on only reducing pain and further consequences [8]. Furthermore, in chronic LBP, there is also a problem in the pattern of muscular activation that influences the brain and vice versa. Despite the aspect of pain perception, there is maladaptive plasticity in chronic low back pain patients could be associated with disorders of volitional activation of trunk/pelvis muscles and alterations of their anticipatory motor patterns for postural control [9, 10]. This might lead to asymmetrical changes in the cross-sectional area of the multifidus [MF] muscles located at the lumbar spine [11].

Though there are numerous biological factors that contribute to LBP, psychological factors may play an unexpectedly large role in some patients with chronic LBP [12]. New insights are coming from different fields of research, with a lot of work being done in searching for the factors involved in persistent back pain [12]. There are many established factors such as physical, biological, cognitive, behavioral, social, and occupational associated with poor prognosis following the onset of musculoskeletal pain [13–15]. Hence, the recent recommended treatment approach is to discourage use of pain medication, steroid injections, and spinal surgery and instead promote physical and cognitive behavioral therapy [16]. Evidences support that psychological factor in the form of kinesiophobia negatively influences many treatment effects for patients with CLBP [17, 18].

Kinesiophobia is described as an excessive, unreasonable, and crippling fear of performing a physical motion due to a feeling of vulnerability to a painful injury or reinjury [19]. Clinical studies suggest that an exaggerated negative cognitive response toward actual pain known as pain catastrophizing and fear of movement/(re)injury (kinesiophobia) is important in the etiology of chronic low back pain and associated disability [20]. These findings are consistent with a cognitive-behavioral perspective that underscores the importance of maladaptive interpretations of bodily sensations [20].

The mechanism can be described as follows: persons who catastrophically misinterpret innocuous bodily sensations, including pain, are likely to become fearful of pain, which results in at least two processes. First, pain-related fear is associated with avoidance behaviors and the avoidance of movement and physical activity in particular. Avoidance also means withdrawal from rewarding activities such as work, leisure, and family. Second, pain-related fear is associated with increased bodily awareness and pain hypervigilance. Hypervigilance, depression, and disuse are known to be associated with increased pain levels and hence might exacerbate the painful experience. This model is used to develop successful treatments [20–22].

Thus, kinesiophobia is correlated to pain-related interference and triggers motor activity changes that influence activities related to pain and pain-related disability management and control [18]. The prevalence of kinesiophobia in chronic pain varies from 50 to 70% [23]. A higher degree of kinesiophobia is correlated with higher levels of perceived pain [24] and lower level re-entry into pre-injury activities for all [CMP] chronic musculoskeletal pain conditions [25]. Thus, clinicians should consider kinesiophobia as an important factor in their preliminary assessment of patients with chronic LBP [18].

Kinesiophobia may produce a wide variety of physical and psychological effects that indirectly influence back pain to be maintained or recur or cause changes in the somatosensory system [26–28]. Studies in the past reported that patients with LBP had poorer ability to sense a change in lumbar position than control subjects [29–33]. Evidence reported that higher levels of pain-related fear are significantly associated with reduced amplitudes of movement and larger muscle activity and were consistent across subgroup and moderation analyses [27, 34]. Recent systematic reviews reported a moderate to strong evidence of associations between a greater degree of kinesiophobia, disability, and poorer quality of life in CMP. However, there was lack of consensus as there was heterogeneity present between all included studies in the systematic reviews in terms of population, outcome measures, pain conditions, and statistical parameters. Hence, an efficient comparison could not be made between their included studies. Moreover, none of the included studies specifically evaluated the possible mediating effect of kinesiophobia in CMP. Furthermore, confounding variables were not always explored in all included studies [18, 35]. Recent researches exploring the influence of kinesiophobia on CLBP and its various outcome are in the infant stage.

Chronic LBP is also associated with decreased endurance of the trunk extensor muscles [TE]. In addition, studies reported TE in chronic LBP participants to be significantly weaker than asymptomatic participants. The multi-factorial dysfunctions consistently reported in literature is the deconditioning of the lumbar extensor musculature, i.e., thoracic and lumbar erector spinae, multifidus, and quadratus lumborum [36, 37].

Long-term mechanical low back pain (LBP) results in inhibition and atrophy of the deep segmental muscles such as multifidus and overactivity of the longer superficial muscles of the trunk with resultant decreased dynamic activity and increased fatigability [38, 39]. Though the muscular endurance is reported to be affected in the patient with CLBP, no studies have explored the impact of kinesiophobia on lumber muscle endurance in patient with CLBP [40, 41] against asymptomatic subjects.

Moreover, in the spine, proprioceptive information is provided by structures present in the spinal ligaments, facet joints, intervertebral discs [42], and paraspinal muscles [43]. Muscle spindle density is high in deep paraspinal rotators, which are small muscles spanning one or two segments of the spine act as kinesthetic sensors that monitor trunk position and movement. It is these muscle receptors that are more likely responsible for information in the midrange of trunk motions [44]. Deficits in proprioception in lower back pain [LBP] have generally been attributed to impaired afference from paraspinal muscle spindle or changes to its central processing. Trials with visual feedback demonstrated that participants with and without CLBP could perform the task accurately. Yet, when visual feedback was removed, participants with CLBP matched the force less accurately than control participants and undershot the target force [42–44].

To the best of our knowledge, till date there are no studies assessing the relationship between kinesiophobia, lumbar endurance, and lumbar position sense in subjects with CLBP. Therefore, the current study aims to compare the impact of kinesiophobia on lumbar extensor endurance, and position sense in patient with CLBP and asymptomatic individuals. Secondarily, we aim to examine the association between kinesiophobia and lumbar extensor endurance, position sense, pain intensity, and functional ability in patients with CLBP. Thirdly, we aim to assess the degree of association with various factors on CLBP, lumbar endurance, and position sense. Therefore, we hypothesized that kinesiophobia would impact the lumbar position sense and lumbar endurance as well.

